## Abstract

**Introduction:**

Survivors of acute pancreatitis (AP) have shorter overall survival and increased incidence of new-onset cardiovascular, respiratory, liver and renal disease, diabetes mellitus and cancer compared with the general population, but the mechanisms that explain this are yet to be elucidated. Our aim is to characterise the precise nature and extent of organ dysfunction following an episode of AP.

**Methods and analysis:**

This is an observational prospective cohort study in a single centre comprising a University hospital with an acute and emergency receiving unit and clinical research facility. Participants will be adult patient admitted with AP. Participants will undergo assessment at recruitment, 3 months and 3 years. At each time point, multiple biochemical and/or physiological assessments to measure cardiovascular, respiratory, liver, renal and cognitive function, diabetes mellitus and quality of life. Recruitment was from 30 November 2017 to 31 May 2020; last follow-up measurements is due on 31 May 2023. The primary outcome measure is the incidence of new-onset type 3c diabetes mellitus during follow-up. Secondary outcome measures include: quality of life analyses (SF-36, Gastrointestinal Quality of Life Index); montreal cognitive assessment; organ system physiological performance; multiomics predictors of AP severity, detection of premature cellular senescence. In a nested cohort within the main cohort, individuals may also consent to multiparameter MRI scan, echocardiography, pulmonary function testing, cardiopulmonary exercise testing and pulse-wave analysis.

**Ethics and dissemination:**

This study has received the following approvals: UK IRAS Number 178615; South-east Scotland Research Ethics Committee number 16/SS/0065. Results will be made available to AP survivors, caregivers, funders and other researchers. Publications will be open-access.

**Trial registration numbers:**

ClinicalTrials.gov Registry (NCT03342716) and ISRCTN50581876; Pre-results.

Strengths and limitations of this studyProspective cohort study with molecular mechanistic observations.In-depth clinical and physiological annotation of multiomics data.Drop-out rates in long-term prospective acute pancreatitis (AP) studies is largely unknown.Potential participants with severe AP may lack capacity for consent and recruitment may therefore be slower in this group.

## Introduction

Acute pancreatitis (AP) is an inflammatory disease of the pancreas usually triggered by gallstones or excess alcohol consumption. The incidence of AP ranges from 13 to 45 per 100.00 individuals, is increasing,^1^ and varies between nations. For example, USA, Finland, Scotland and Germany report higher incidences than England and The Netherlands.^2–5^ AP triggers a cascade of inflammatory events causing cell damage and release of damage-associated molecular patterns that trigger inflammation and cytokine release, initiating a systemic inflammatory response resulting in multiple organ dysfunction syndrome (MODS) in one in five individuals. AP-MODS has a 21% fatality rate during the index episode, and overall in-hospital mortality is 5.2% in Scotland.^6 7^ AP is graded into mild, moderate and severe, based on local and systemic determinants of severity as per the most recent AP classifications (Determinant-based Classification^8^ and Revised Atlanta Classification).^9^ Organ failure in AP most commonly affects the respiratory, renal and cardiovascular systems, but can involve any system.^10^ The pattern of organ failure is difficult to predict and a high level of inter-individual variance is seen, regardless of the aetiology. The molecular mechanisms that explain this inter-individual variation in local and systemic inflammatory processes in AP remain unidentified.^11^ Multiomics analysis of serial time course blood samples has defined molecular patterns in human AP, called endotypes, but the precise relevance of these endotypes to clinical and therapeutic decision-making is not yet determined.^12^

Recently published data from a retrospective analysis of patients with AP has shown that the early development of MODS is associated with an increased mortality rate up to 10 years after the index presentation.^6^ This strongly suggests that MODS in acute pancreatitis (AP-MODS) has a persistent and deleterious impact on patients’ physiological status, though the exact nature of this pathology remains to be characterised. Existing studies indicate that most deaths are the result of cardiovascular, pulmonary, digestive or malignant disease.^13–16^ In addition, the new onset of diabetes (type 3c diabetes mellitus (DM)) or impaired glucose tolerance, peripheral neuropathy and exocrine dysfunction have been documented as sources of morbidity in the years following the index attack of severe AP.^16 17^ Patients with alcohol-induced pancreatitis may be at particularly increased risk of progression to chronic pancreatitis,^14^ however the development of long-term complications is likely to be influenced by multiple, and as-yet unconfirmed, factors.

The aim of this observational clinical cohort study is to characterise the nature and extent of the pathophysiological impact of severe AP on organ function over the first 3 years after the index AP episode and define the long-term deleterious effect of severe AP. This will be achieved by prospectively measuring organ system function in patients recruited during a hospital admission with AP and at set time intervals thereafter. We will obtain an in-depth assessment of patients’ health at presentation, and at 3 months and 36 months after the first episode of AP using markers of organ function and/or disease in the peripheral blood. In a nested cohort within the main study cohort, we will conduct cardiorespiratory evaluation tests (including exercise testing), specialised blood tests of the immune system, tests for precision medicine, and imaging to assess structure and function of key organ systems.

The results of this study will inform the design of future interventions designed to improve the long-term prognosis of patients.

## Methods

### Ethical approval

The study will be conducted in accordance with the principles of the International Conference on Harmonisation Tripartite Guideline for Good Clinical Practice. This study has been reviewed and been given a favourable opinion by the South-East Scotland Research Ethics Committee, under the application numbers: REC Number 16/SS/0065; IRAS Number 178615 and R&D approval Lothian R&D Number 2016/0152.

### Study design

This is an observational prospective nested cohort study. The overall cohort is the population presenting with AP that meets the eligibility criteria. For the nested cohort of the study, a stratified block design is to be used to recruit equivalent numbers of patients with AP-MODS vs AP without MODS.

### Setting

Single centre academic hospital setting—Royal Infirmary of Edinburgh, NHS Lothian and the Edinburgh Clinical Research Facility, Royal Infirmary of Edinburgh, UK.

### Duration

Recruitment started on 30 November 2017 and is scheduled to end on 31 May 2020. The cohort assessment will comprise of three study visits. In-depth assessments of a participant’s health at presentation, at 3 months and at 36 months follow-up study visit will be obtained. Additional cardiorespiratory evaluation tests, specialised blood tests of the immune system, tests for precision medicine, and imaging to assess structure and function of key organ systems will be conducted in a nested cohort of participants.

### Intervention

This is a prospective study examining patient outcomes and trends in patients’ physiological status after an index event. Therefore, no intervention or randomisation is proposed.

### Measurements

#### Primary endpoint

Overall cohort: to define the incidence of new-onset type 3c DM in patients with AP, compared with the age-matched population of Scotland.Nested cohort: to define the baseline change in pancreatic fibrosis index measured by multiparameter MRI between 3 months and 36 months after recruitment.

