#### Summary of clinical data to be collected

All participants in the overall and nested cohorts will have the following data collected:

Demographic and clinical background information.Information regarding the acute presentation.Organ function assessment at recruitment, 3-month and 36-month follow-up study visit:

Overall cohort:Full peripheral venous blood profiling, including cardiac biomarkers, standard biochemistry profiling, and samples retained for miRNA profiling, cytokines, telomere length, metabolomic profiling, proteomic profiling, transcriptomic profiling, genomic profiling, leucocyte subset analysis by flow cytometry.Biochemical markers of organ function in urine and samples retained.Pancreatic exocrine function test in stool (faecal elastase).Nutritional assessment.Oral glucose tolerance test at 3-month and 36-month follow-up study visit (with the exception of insulin dependent diabetics who will have random blood glucose measured only).12 lead ECG, blood pressure.Peripheral SpO_2_.Sway balance app non-invasive muscle function tests, 6-minute walk test.Self-administered Patient QuestionnaireGastrointestinal Quality of Life Index.SF-12 Quality of Life.Montreal Cognitive Assessment.Nested cohorts:Pulse wave analysis (with salbutamol inhaler); transthoracic echocardiography.Spirometry and gas transfer.Cardiopulmonary exercise (CPEX) testing.Multiparameter MRI assessment of liver and pancreas.

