#### Nutritional assessment

Participants will have their height and weight measured in order to calculate their body mass index, as well as bioimpedance analysis±upper arm anthropometry to assess percentage body fat and lean tissue mass. Participants will also be asked to keep a 24 hours food diary to assess whether their calorie and protein intake is sufficient for their nutritional needs at all three study visits. Trace element, including zinc, selenium and vitamin B_12_ levels and other relevant micronutrients will be measured in peripheral venous blood.

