#### Sample size calculation

Overall sample size calculation has been performed to illustrate how well we will be able to estimate the annual incidence of type 3c diabetes in patients with AP with varying sample sizes.^25 26^ The incidence of type 3c DM was chosen for the purposes of establishing a prospective cohort size because it is specific, measurable, clinically relevant and offers a practice-changing opportunity for intervention. With a sample of 323 we would have 80% power to be able to show a difference from the incidence of DM in the general population (6%) if we observed an incidence in the cohort of 10% or greater. Moreover, this sample size will support the evaluation of the secondary endpoints, allowing us to adjust for any confounding factors.

Nested cohort sample size has been calculated to detect the difference in the 3 months to 36 months change in pancreatic fibrosis index between those with AP with MODS and those with AP without MODS based on Banerjee *et al* estimates of fibrosis index using multiparameter MRI.^27^ Based on a sample size of 20 participants per group, using a two-sided two-sample test with a 5% level of significance and 80% power, we would be able to detect an effect size of 0.909 (where the effect size is the absolute difference in means divided by common SD). To allow for potential dropouts in this part of the study (death, withdrawal) a minimum sample size of 25 individuals will be recruited for the nested cohort.

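### The primary diabetes comparison names age as its only matching factor, so a different sex or deprivation mix in AP patients would bias it, in a direction the protocol does not settle

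*Protocol article*

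**What the plan says.** Under Primary endpoint, the protocol article sets the aim for the overall cohort, and fixes the comparator in the same sentence: "to define the incidence of new-onset type 3c DM in patients with AP, compared with the age-matched population of Scotland". No other matching or standardising factor is named there.

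Three other places bear on the comparison, and none of them widens it:

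- **Statistical analysis plan.** Annual incidence is to be given as a percentage with a 95% CI. The covariates listed (aetiology, severity, medical background) are attached to the nested-cohort fibrosis index. Sex, deprivation and BMI are not among them.
- **Sample size calculation.** The cohort is sized against a single general-population diabetes figure of 6%, not broken down by age or sex: "With a sample of 323 we would have 80% power" to show a difference "if we observed an incidence in the cohort of 10% or greater". Adjustment for confounding is mentioned only in connection with the secondary endpoints.
- **Data collected.** All participants provide "Demographic and clinical background information", and under Nutritional assessment "Participants will have their height and weight measured in order to calculate their body mass index". The article does not itemise sex or deprivation.

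**The concern.** Diabetes incidence can vary with sex and deprivation as well as age. Matching on age makes the two sides alike in age and nothing else. If the AP cohort has a different sex or deprivation mix from Scotland as a whole, its expected diabetes rate without pancreatitis differs from the age-matched reference, and that difference is added to or subtracted from whatever is observed.

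In a study with individual controls, a regression model could deal with this later. Here the comparator is described only as a population. A model fitted within the cohort can compare one AP patient with another, but it cannot correct the external reference. The correction has to be built into the expected number of cases.

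What is at stake is the reading of the primary result. The target difference is four percentage points (10% against 6%), so a modest error in the reference takes up a material part of it.

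**Working it through.** **1. Reproduce the protocol's figure.** Inputs from Sample size calculation: p0 = 0.06, p1 = 0.10, power 80%. The significance level for the overall cohort is not stated. Two-sided 5% is assumed, because the nested-cohort calculation uses it.

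n = [(1.960 × √(0.06 × 0.94) + 0.842 × √(0.10 × 0.90)) / 0.04]² = 322.16, rounded up to 323.

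This matches, so the stated figure is that of a one-sample test of the cohort against a fixed 6%. A two-sample calculation would need 721 per group.

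**2. Critical count.** The score test declares an excess when the observed proportion passes 0.06 + 1.960 × √(0.06 × 0.94 / 323) = 0.0859. Since 0.0859 × 323 = 27.7, that means 28 or more cases.

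**3. Effect of a shifted background rate.** Let k be the ratio of the cohort's diabetes rate in the absence of any AP effect to the reference. The protocol gives no value for k; those below are assumptions. The probability of a declared excess is P(X ≥ 28) with X ~ Binomial(323, 0.06k):

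| k | Background rate | Excess declared with no AP effect |
|---|---|---|
| 1.0 | 6.0% | 3.4% |
| 1.1 | 6.6% | 8.7% |
| 1.2 | 7.2% | 17.9% |
| 1.3 | 7.8% | 30.8% |

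The first row exceeds the nominal 2.5% upper tail only because the count is discrete. The normal approximation gives 2.5%, 7.5%, 16.7% and 29.8%.

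**4. The other direction.** Suppose k = 0.9 and AP truly multiplies the rate by 10/6. The cohort rate is then 0.9 × 6% × 10/6 = 9.0%, and P(X ≥ 28) is 61.1%, against 81.2% at the planned 10%. A real excess would be missed more often.

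**5. Which k are plausible.** For one binary factor, k = (pc × RR + 1 − pc) / (pp × RR + 1 − pp), where pc and pp are its prevalence in the cohort and the population, and RR is its rate ratio for diabetes. All inputs are assumed.

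| Factor | pc | pp | RR | k |
|---|---|---|---|---|
| Male sex | 55% | 49% | 1.3 | 1.165 / 1.147 = 1.02 |
| Male sex | 65% | 49% | 1.6 | 1.390 / 1.294 = 1.07 |
| Male sex | 40% | 49% | 1.3 | 1.120 / 1.147 = 0.98 |
| Male sex | 40% | 49% | 1.6 | 1.240 / 1.294 = 0.96 |
| Most deprived fifth | 30% | 20% | 1.5 | 1.15 / 1.10 = 1.05 |
| Most deprived fifth | 40% | 20% | 2.0 | 1.40 / 1.20 = 1.17 |

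The sign for sex depends on whether the cohort has more or fewer men than the population, which the protocol does not say.

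No range is given for obesity. The endpoint is type 3c diabetes, while the 6% reference is for diabetes without a type. If weight-related type 2 cases are not counted in the cohort, obesity would not raise its count in the way this formula assumes.

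**The case against.** The strongest reply has four parts.

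- **Detail is left to the SAP.** The article defers full analysis details to a separate plan, and naming age does not exclude other factors. This is fair for strata and interval method, and further standardisation may be specified there. It does not remove the point, because the published definition of the primary endpoint makes a choice and names age alone.
- **The analysis is descriptive.** A reader might infer that any imbalance will be counted as diabetes caused by AP. The protocol does not say so: it plans an incidence with a CI, and nowhere attributes the excess over the population to AP. The general aim in the Introduction, about lasting harm from severe AP, is not tied to this comparison. What stands against the reply is that the cohort is powered to show a difference, so the comparison is more than a description.
- **The bias is assumed.** A reader might also infer that the false-positive rate is raised, because AP patients are more often male, deprived or obese. The documents do not support that. They give no such distributions, and with 40% men the sex ratio falls below 1. Nor do they define the cohort as gallstone and alcohol AP: the Introduction calls these the usual triggers, and the inclusion criteria set no limit on cause. This part of the reply stands in full.
- **The illustration uses a crude rate.** The 6% is a planning figure and not an age-matched expected rate. The calculation shows how sensitive such a test is to a wrong reference. It does not measure the error left by age matching. This also stands.

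**Conclusion.** The point holds in a limited form. The primary comparison names age alone, nothing in the article adds sex or deprivation to it, and an external population comparator means that the gap cannot be closed by modelling the cohort. Whether a bias exists, which way it runs and how large it is cannot be determined from the protocol.

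The figures of about 9% and 18% false excess (against 3.4%) are illustrations that rest on three assumptions: a two-sided 5% score test, a 6% reference, and a background rate 10% or 20% above it. The difference between a type 3c outcome and a reference for diabetes of unstated type is a further comparability gap in the same comparator. It could pull the result downward, and there is no reason to expect the two to cancel.

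The sample size of 323 reproduces exactly and is not in question.

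**What to change.** In Primary endpoint, replace the age-matched comparator by an expected number of cases, standardised to the cohort's age and sex and, where national rates exist, to area deprivation. Use the same diabetes definition for the cohort and the reference rates. Report observed/expected with an exact Poisson 95% CI.

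Where reference rates for a factor cannot be had, which may include BMI, state that the comparison is descriptive and is not to be read as an effect of AP.

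The cost is small. Demographic data and BMI are already collected, so no extra visit is needed, although the case report form should be checked for sex and an area deprivation measure. Population rates by sex and deprivation must be obtained; their availability is assumed. The reported excess may turn out smaller than against an age-only reference.

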#### Secondary endpoints

Secondary end-points in the study will be experimental and observational, and will define explicitly, or be preliminary exploratory studies investigating:

Genomic predictors of AP severity and resolution of inflammation.miRNA signatures of disease severity and resolution.Metabolomic profiling of AP resolution, and development of local and systemic complications.Premature cellular senescence as a pathological consequence of AP-MODS.Alteration in immune cell subsets and phenotype as a long-term response to AP-MODS.Cardiovascular and respiratory dysfunction as a legacy of endothelial injury during AP-MODS.

#### Summary of clinical data to be collected

All participants in the overall and nested cohorts will have the following data collected:

Demographic and clinical background information.Information regarding the acute presentation.Organ function assessment at recruitment, 3-month and 36-month follow-up study visit:

Overall cohort:Full peripheral venous blood profiling, including cardiac biomarkers, standard biochemistry profiling, and samples retained for miRNA profiling, cytokines, telomere length, metabolomic profiling, proteomic profiling, transcriptomic profiling, genomic profiling, leucocyte subset analysis by flow cytometry.Biochemical markers of organ function in urine and samples retained.Pancreatic exocrine function test in stool (faecal elastase).Nutritional assessment.Oral glucose tolerance test at 3-month and 36-month follow-up study visit (with the exception of insulin dependent diabetics who will have random blood glucose measured only).12 lead ECG, blood pressure.Peripheral SpO_2_.Sway balance app non-invasive muscle function tests, 6-minute walk test.Self-administered Patient QuestionnaireGastrointestinal Quality of Life Index.SF-12 Quality of Life.Montreal Cognitive Assessment.Nested cohorts:Pulse wave analysis (with salbutamol inhaler); transthoracic echocardiography.Spirometry and gas transfer.Cardiopulmonary exercise (CPEX) testing.Multiparameter MRI assessment of liver and pancreas.

#### Venous blood, urine and stool sampling

Blood samples will be obtained from each study participant at each of the three study visits for organ function and specialist assays. A urine sample and a stool sample will be obtained at each of the three visits.

#### Nutritional assessment

Participants will have their height and weight measured in order to calculate their body mass index, as well as bioimpedance analysis±upper arm anthropometry to assess percentage body fat and lean tissue mass. Participants will also be asked to keep a 24 hours food diary to assess whether their calorie and protein intake is sufficient for their nutritional needs at all three study visits. Trace element, including zinc, selenium and vitamin B_12_ levels and other relevant micronutrients will be measured in peripheral venous blood.

#### Oral glucose tolerance test

At the 3-month and 36-month follow-up study visits an oral glucose tolerance test will be performed. Participants attending the research site for physiological testing will be asked to attend in a fasted state. On arrival participants will have the baseline blood sample taken (using the same venepuncture as other tests above as appropriate), be given a standard 75 g anhydrous glucose in cold water or Polycal (113 mL) which is more palatable and will be followed by 150 mL water (total volume should be 250–300 mL). After 120 min, a second blood sample will be taken (using the same venepuncture as other tests above as appropriate) to measure blood glucose.

An oral glucose tolerance test will not be performed in participants with insulin dependent diabetes. Instead a random glucose sample will be taken at these visits.

#### Non-invasive muscle function testing, Sway balance test, 6-minute walk test

Manual Muscle Testing will be performed once per visit to assess muscle strength. This will follow structured protocols used to assess muscle strength in survivors of critical illness.^18^ The strength of muscles involved in shoulder abduction, elbow flexion, wrist extension, hip flexion, knee extension and ankle dorsiflexion will be graded according to the Medical Research Council muscle strength scoring system.

Participants will undergo an assessment of balance and postural stability at each visit. Testing will follow a validated protocol using the Sway Balance mobile testing system.^19 20^ Participants will be asked to hold a mobile device against their chest while completing a series of stances: standing with both feet together, standing with one foot behind the other, and standing on each leg in turn.^20^ Each stance is held for 10 s with the eyes closed. The Sway Balance application will generate a balance score, based on detection of alterations in position during each stance.

A 6-minute walk test will be done, according to standard protocols.^21^

